#### 2.7.2. Control group

Participants included in the control group in a randomized manner will be instructed to maintain their usual medical treatment and daily routines during the experimental intervention period, which did not include structured exercise. After the end of the protocol, the patients were re-evaluated and invited to receive the training program. After the end of the protocol and the re-evaluation, control group participants will be given the opportunity to perform the training program.

### 2.8. Retention and adherence

To maintain adherence, individualized attention will be prioritized during the session and especially the care regarding pain control of everyone at the beginning, during and at the end of each session. In case of absence, the participant will be contacted for information regarding his/her health status or other reasons. In case of withdrawal from the program, the reason will be investigated to be identified at the end of the study.

### 2.9. Sample size calculation

The G-power software was used to detect a moderate effect size (partial eta squared of 0.09) in the intra/inter-group comparison. Considering an alpha value of 5%, the total number of participants should be 24 so that the power of the results is 90%. Considering a 20% of dropout risk, a minimum of 30 participants will be recruited (15 for each group).

### 2.10. Statistical analysis

SPSS software will be used. To verify normality either the Shapiro-Wilk test (n < 30) will be used, and the equality of variances will be assessed by the Levene test. If the data, follow a normal distribution inter-group and intra-group differences will be calculated by repeated measures analysis of variance (ANOVA). If the data do not follow a normal distribution, the Kruskal-Wallis test will be calculated for between-group differences and the Friedman test for intra-group differences. To calculate the effect size, Cohen's test (intra-group comparison) will be used, and the between-group variance (partial eta squared) will be estimated. To verify the reliability of the tests and their measurements, the coefficient of variation and the intraclass correlation coefficient will be calculated. Finally, to evaluate the relationships between variables, Pearson's correlation coefficient will be calculated. The significance level will be set at 0.05.

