## 2. Materials and methods

### 2.1. Study design

The present study protocol refers to a single-blind, randomized controlled trial, developed according to Standard Protocol Items: Recommendations for Interventional Trials (SPIRIT) (34). The volunteers will be allocated randomly to the intervention group that will receive the exercise program or the control group. A staff member not involved in the study will be responsible for the randomization based on a computer-generated random number. The intervention program will last 12 weeks, consisting of 8 weeks of strength training plus 4 weeks of no training for the intervention group. The 1-month period will serve to evaluate how long the effects of the training will still be present after the training has ceased. The flow chart of the study design is represented in Figure 1.

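### The three-visit repeated-measures ANOVA tests neither of the trial's two questions directly and drops anyone with a missing visit; a baseline-adjusted mixed model gives a modest gain from the same data

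*Protocol article*

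**What the plan says.** Section 2.10 (Statistical analysis) fixes the software, "SPSS software will be used", and the method. If the data are normal, "inter-group and intra-group differences will be calculated by repeated measures analysis of variance (ANOVA". It adds that "The significance level will be set at 0.05". No visit, contrast or baseline covariate is named.

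Section 2.5 has both groups assessed again in the week after the 8 training weeks, and once more after 4 weeks off training. With baseline that makes three visits. Section 2.1 gives the last visit its own purpose: "The 1-month period will serve to evaluate how long the effects of the training will still be present". The Introduction states the main aim as the effect of the 8-week online programme on balance, neuromuscular performance and symptoms.

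Section 2.9 sizes the trial for a "moderate effect size (partial eta squared of 0.09) in the intra/inter-group comparison". It continues: "Considering an alpha value of 5%, the total number of participants should be 24 so that the power of the results is 90" (per cent), and then "Considering a 20% of dropout risk, a minimum of 30 participants will be recruited (15 for each group").

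**The concern.** One ANOVA covering within-group change as well as between-group differences must carry baseline as a level of time. Two consequences follow.

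- **Targeting.** With two arms and three visits, the group-by-time test has 2 numerator degrees of freedom. It rejects for any difference in the shape of the two profiles. It does not isolate the arm difference after training or the arm difference 4 weeks later, which are the two questions the design sets up.
- **Missing visits.** Standard SPSS repeated-measures ANOVA deletes a participant listwise if any visit is missing. This is a property of the procedure; the article does not state it. A participant assessed after training but not at the last visit would then contribute nothing to the post-training comparison.

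What is at stake is power and a directly interpretable estimate in a trial of about 30 people.

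**Working it through.** **Step 1: reproduce the plan's figure.** Inputs from section 2.9: partial eta squared 0.09, alpha 0.05, power 90%, N = 24, dropout 20%. Assumed, because not stated: correlation between visits rho = 0.5, sphericity, and the G*Power default effect-size convention.

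- f² = 0.09/0.91 = 0.0989, so f = 0.3145.
- Interaction, k = 2 groups, m = 3 visits: lambda = f² × N × m/(1 − rho) = 0.0989 × 24 × 3/0.5 = 14.24.
- Degrees of freedom: (k − 1)(m − 1) = 2 and (N − k)(m − 1) = 44. Power = 0.914, and 24 is the smallest even N reaching 90%.
- 24/(1 − 0.20) = 30.

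Two visits would need 30 and a between-groups effect 74 (three visits) or 82 (two visits). The pure time effect has the same formula as the interaction. The stated 24 therefore fits an omnibus three-visit test in completers.

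**Step 2: translate to an arm difference.** Let the arm differences be 0 at baseline, d SD after training and k·d at the last visit, where k is now the fraction of the effect kept. Under compound symmetry with SD 1,

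lambda = (N/4) × d² × (2/3)(1 − k + k²)/(1 − rho).

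With the effect fully kept or fully lost (k = 1 or 0), N = 24 and rho = 0.5, this is 8d². Setting 8d² = 14.24 gives d = 1.33. The term 1 − k + k² is smallest at k = 0.5, so half retention is the least favourable case for the interaction test.

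**Step 3: baseline-adjusted contrast after training.** The residual variance is 1 − rho². The variance of the adjusted difference is (1 − rho²) × (4/N) × (1 + 1/(N − 4)), where the last factor allows for estimating the baseline slope; the t test has N − 3 = 21 df. For d = 1.0 and rho = 0.5: variance = 0.75 × 0.1667 × 1.05 = 0.131, noncentrality = 1/√0.131 = 2.76, power 0.75. The interaction has lambda = 8 and power 0.69 if the effect is fully kept or lost, and lambda = 6 and power 0.55 if half is kept.

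Power, interaction / adjusted contrast, complete data, N = 24:

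| Effect after training; at last visit | rho 0.3 | rho 0.5 | rho 0.7 |
|---|---|---|---|
| 1.33 SD; fully kept or lost | 0.79 / 0.89 | 0.91 / 0.94 | 0.99 / 0.99 |
| 1.0 SD; fully kept or lost | 0.53 / 0.67 | 0.69 / 0.75 | 0.89 / 0.89 |
| 1.0 SD; half kept | 0.42 / 0.67 | 0.55 / 0.75 | 0.79 / 0.89 |

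**Step 4: missing visits.** At 20% loss, 0.20 × 30 = 6 people are incomplete. The timing is not given, so between 0 and 6 of them have a post-training value that listwise deletion would discard. As an illustration, assume random loss of 10% by the post-training visit and 20% by the last. The ANOVA then keeps about 24 people and the contrast about 27. Simulated power (4,000 trials per scenario, 30 randomised, analysis of covariance on everyone with the post-training visit as a stand-in for the mixed model):

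| Effect after training; at last visit | rho 0.3 | rho 0.5 | rho 0.7 |
|---|---|---|---|
| 1.33 SD; fully kept | 0.79 / 0.93 | 0.90 / 0.96 | 0.99 / 0.99 |
| 1.0 SD; fully kept | 0.52 / 0.72 | 0.68 / 0.81 | 0.88 / 0.92 |
| 1.0 SD; half kept | 0.42 / 0.73 | 0.54 / 0.80 | 0.78 / 0.92 |

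With no true effect and rho = 0.5, the rejection rates were 0.054 and 0.051, so both tests hold their level.

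**The case against.** The strongest reply is that this is a preference between valid methods, with a gain that can be nil. At the plan's implied effect with complete data the gain is 3 points at rho 0.5. With the effect fully kept or lost it is nil at rho 0.7, and at rho 0.8 the interaction is marginally ahead (0.98 against 0.97 at 1.0 SD). The large differences appear under half retention, the interaction's worst case. All of this stands and limits the size of the point.

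Some of the gain also needs no new model. A post-training-against-baseline contrast within the ANOVA (1.0 SD, rho 0.5) has variance 2(1 − rho) × 4/24 = 0.167, noncentrality 2.45 and power 0.65. That recovers about half of the distance from 0.55 to 0.75. It is below the 0.69 of the omnibus test when the effect is fully kept, so choosing a contrast alone is not a full answer.

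A further reply is that contrasts and missing-data rules belong in an analysis plan that is not shown. That is fair for their absence. The point rests on the method that section 2.10 does fix.

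Four stronger readings are tempting and not supported:

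- **The ANOVA is invalid.** With complete data it is not.
- **The between-group main effect, diluted by baseline, is the efficacy test.** The article does not say so, and the sample size fits the interaction.
- **Wide variation by sex and age in jump and throw results makes the ANOVA inefficient.** Such stable differences between people raise rho, and the gain then shrinks.
- **The completer analysis is biased.** The Discussion links worsening symptoms to exercise dropout, and section 2.2 discontinues people who change medication, so selective loss is plausible. It is not established. The mixed model relies on missing-at-random and also cannot use anyone without a follow-up.

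**Conclusion.** The point holds as one of efficiency and targeting. The fixed analysis does not directly test either the post-training difference or its persistence, and as usually run in SPSS it discards post-training values from people who miss only the last visit. Six of 30 is a ceiling on that loss. If all dropout falls within the training weeks, no post-training value is lost.

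With complete data, N = 24 and rho 0.5, the gain from the adjusted contrast is 3 points at the plan's implied effect, 6 points at 1.0 SD fully kept or lost, and 20 points at 1.0 SD half kept. It grows at lower rho or when people miss only the last visit. With complete data and the effect fully kept or lost, it is about zero at rho 0.7 or above. These figures rest on compound symmetry, on assumed values of rho and retention, and in the dropout table on loss at random. The document gives none of these.

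**What to change.** For the outcomes now assigned to repeated-measures ANOVA, specify a linear mixed model in SPSS MIXED:

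- Outcome: the post-training and off-training values. Fixed effects: arm, visit, arm × visit and the baseline value.
- REML, unstructured covariance over the two follow-up visits, Satterthwaite or Kenward-Roger degrees of freedom. This has only three covariance parameters, but name a fallback structure in case of non-convergence.
- Main contrast: the arm difference at the post-training visit with its 95% confidence interval. Test of persistence: the arm difference at the off-training visit.
- Analysis set: every randomised participant with at least one follow-up.

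The software, visits and participants stay the same, so the change is one of wording, with three small costs. Within-arm change, which the ANOVA delivered directly, has to be reported separately as a descriptive estimate. The missing-at-random assumption should be stated. Section 2.9 should say that its 24 was derived for a three-visit repeated-measures test, and with what assumed correlation, because it will no longer match the main analysis exactly.

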### 2.4. Randomization

After evaluation of the inclusion and exclusion criteria, the participants eligible to participate in the study will be randomly separated into two groups: the control group (CG): which will have no activities performed; the experimental group (EG): which will follow the strength exercises protocol.

The randomization of the participants will be performed by an individual not directly related to the study. To avoid selection bias, random numbers will be generated by computer; the distribution will be made from a website: www.randomization.com. For the statistical analysis, the researcher in charge will receive the data without identifying the participants to obtain the results in a blinded manner. A randomization with a 1:1 computer-generated will be made for the group allocation.

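### When normality fails, the named fallback tests use no baseline and contain no test of differential change, which costs precision with 12 to 15 per arm

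*Protocol article*

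**What the plan says.** Section 2.10 sets up two routes. A Shapiro-Wilk test decides between them. If the data are normal, "inter-group and intra-group differences will be calculated by repeated measures analysis of variance (ANOVA"). If not, "the Kruskal-Wallis test will be calculated for between-group differences and the Friedman test for intra-group differences". The section names no change score, baseline covariate or rank-based interaction for the second route.

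On effect sizes the same section says "To calculate the effect size, Cohen's test (intra-group comparison) will be used", and adds that partial eta squared will be estimated between groups.

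The design is two arms (section 2.4: "A randomization with a 1:1 computer-generated will be made for the group allocation") assessed at baseline, after the 8 training weeks and again after 4 weeks without training (section 2.5). Section 2.9 sizes the trial to "detect a moderate effect size (partial eta squared of 0.09) in the intra/inter-group comparison": 24 evaluable participants, 30 recruited.

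**The concern.** The question is whether the exercise arm changes differently from the control arm. A two-arm, three-visit repeated measures ANOVA supplies that test as its group-by-time term, although the article does not name the term. The fallback has no counterpart:

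- Friedman is run inside one arm. It can show that scores moved over time in that arm, but it cannot compare arms.
- Kruskal-Wallis compares levels between arms. As written, it is applied neither to change from baseline nor with adjustment for baseline.

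So a preliminary normality test decides, outcome by outcome, whether the baseline measurement contributes to the comparison of arms. The outcomes in Table 1 include bounded 0-10 and 0-100 scores and a pressure-centre measure, so some may well take the fallback route. With 12 evaluable or 15 recruited participants per arm, little precision can be spared.

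**Working it through.** **1. The plan's own sample size.** Inputs from section 2.9: partial eta squared 0.09, alpha 0.05, power 90%, N = 24, dropout 20%. Assumed, because not stated: correlation between visits rho = 0.5 and sphericity (epsilon = 1). Three visits (m = 3) and two arms (k = 2) come from sections 2.4 and 2.5.

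- f² = 0.09/0.91 = 0.0989, so f = 0.3145.
- Group-by-time test: lambda = f²·N·m/(1 − rho) = 0.0989 × 24 × 3/0.5 = 14.24, with df (k − 1)(m − 1) = 2 and (N − k)(m − 1) = 44. Power is 91.4%, and 24 is the smallest even N that reaches 90%.
- Dropout: 24/(1 − 0.20) = 30.

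Both stated figures reproduce. The within-subject time test has the same df and lambda with two arms, so it gives the same N. The between-group main effect would need 74 and has 43.8% power at 24. The figure 24 therefore fits the interaction but does not prove that the interaction was the basis.

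**2. Is the fallback's between-arm test valid?** Simulation with 3,000 trials per setting, normal outcomes with SD 1 and rho 0.5. Rejection rates of Kruskal-Wallis on post-training values when the arms do not differ:

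| Truth | 12 per arm | 15 per arm |
|---|---|---|
| No change in either arm | 5.8% | 4.9% |
| Both arms improve by 0.7 SD | 4.6% | 4.9% |

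The level is close to the nominal 5%. Monte Carlo error is at most sqrt(0.25/3000), about 0.9 percentage points.

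**3. What does ignoring baseline cost?** For normal data, the variance of the between-arm difference, relative to a comparison of post values (1), is 2(1 − rho) for change scores and 1 − rho² with baseline adjustment:

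| rho | Post value | Change | Baseline-adjusted |
|---|---|---|---|
| 0.3 | 1 | 1.40 | 0.91 |
| 0.5 | 1 | 1.00 | 0.75 |
| 0.7 | 1 | 0.60 | 0.51 |

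Simulated power at 12 per arm, true difference 1.0 SD:

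| rho | Kruskal-Wallis, post values | Rank ANCOVA |
|---|---|---|
| 0.3 | about 62-65% | about 64% |
| 0.5 | about 63% | about 71% |
| 0.7 | about 62-65% | about 85% |

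The loss is negligible at rho 0.3, about 8 points at 0.5 and 20 points or more at 0.7. The results at 0.5 and 0.7 were similar for normal and lognormal data.

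The assumed 1.0 SD is not far from the design effect. For a gain held at both later visits, f = 0.3145 corresponds to f × sqrt(18) = 1.33 SD at rho 0.5. Holding lambda constant at rho 0.7 gives 1.33 × sqrt(0.3/0.5) = 1.03 SD. At those effects and 12 per arm:

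| | ANOVA group-by-time | Kruskal-Wallis, post | Kruskal-Wallis, change |
|---|---|---|---|
| rho 0.5 (1.33 SD) | 90.8% | 86.5% | 86.5% |
| rho 0.7 (1.03 SD) | 90.9% | 64.6% | 86.4% |

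**4. Baseline imbalance.** The standard error of the baseline difference is sqrt(2/12) = 0.41 SD at 12 per arm and sqrt(2/15) = 0.37 SD at 15, so sizeable chance differences are ordinary. If the arms truly differ by 0.7 SD throughout and nothing changes, Kruskal-Wallis on post values rejects in 36% (12 per arm) or 41% (15 per arm), and on change in 4.5% or 5.3%. This shows how the test responds to a standing difference. It is not the trial's error rate: randomisation produces no systematic shift. A chance imbalance of 0.7 SD carries forward on average only as rho × 0.7 = 0.35 SD at rho 0.5, and the rates in step 2 already average over chance imbalance.

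**The case against.** **A condensed article may leave the analysed variable open.** Section 2.10 does not say what enters Kruskal-Wallis, and a fuller plan might apply it to change. This stands in part. But the article itself fixes the fallback tests, and change scores would be only a partial remedy: they gain nothing at rho 0.5 and lose precision below it.

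**The stated between-arm test is valid.** This stands, and it limits the point to precision.

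**The power gain depends on unknowns.** This also stands. No correlation is given, and the gain vanishes at rho 0.3. Adjustment on the raw scale can do worse: for lognormal data with sigma 1 and rho 0.5, ordinary ANCOVA has about 50% power against 62% for Kruskal-Wallis. That is a reason to adjust on ranks.

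**A stronger reading that the text does not support.** A reader might infer that efficacy would be concluded when Friedman is significant in the exercise arm but not in the control arm. Under equal true improvement of 0.5-0.8 SD, the two Friedman tests disagree in 43-50% of simulated trials at 12 per arm, and only the exercise arm is significant in 22-25%. The plan states no such rule. It assigns between-group differences to Kruskal-Wallis and also plans a between-group effect size. Those percentages are not this plan's error rate. They show only why the decision rule should be written down.

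**The normality gate.** A reader might add that Shapiro-Wilk, run on each of six arm-by-visit cells, would often reject by chance (1 − 0.95^6 = 26%). The article does not say that it is run cell by cell or that one rejection triggers the switch. Where the test misses skew, the analysis stays with the ANOVA, which has the interaction.

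**Conclusion.** The point holds as a loss of precision. For non-normal outcomes the article's named tests drop the group-by-time comparison that the ANOVA route contains, and as written they make no use of the baseline already collected. The between-arm test that remains is valid, with about 5-6% type I error in simulation.

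The forgone power depends on the assumed correlation: close to nothing at rho 0.3, and from about 62-65% up to about 85% at rho 0.7. These figures rest on 12 per arm and an assumed difference of 1.0 SD.

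It should not be claimed that N = 24 was calculated for the interaction. That is plausible under rho 0.5 and sphericity, but the within-subject test gives the same number. This should be fixed, but it does not make the trial's conclusions invalid.

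**What to change.** In section 2.10, for outcomes that fail the normality check, replace Kruskal-Wallis with a baseline-adjusted between-group rank analysis at each of the two post-baseline visits. Rank ANCOVA does this: rank baseline and follow-up over both arms, then compare arms on follow-up rank with baseline rank as covariate. A permutation version of the baseline-adjusted model is an alternative, preferably on ranks where skew is strong.

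Add one sentence stating that a training effect is concluded only from this between-arm contrast, and that Friedman results and within-group Cohen's d are descriptive support.

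The cost is two or three sentences of text and a little more analysis syntax. No extra participants, visits or measurements are needed. The change is best made before outcome data are seen, so that the choice of test cannot appear to follow the results.

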It is known that neuromuscular alterations caused by fibromyalgia can cause a risk of disability, as well as an increased risk of falls and injuries (28–30). For this reason, among the different training programs that were assessed, muscle strength training may be essential in combating or even preventing the onset of such issues. However, there is still weak evidence and some studies have focused on the effects of strength training on this population. Indeed, there are still some gaps in the literature regarding the training type and other variables, such as intensity and duration of practice (14, 31–33). Furthermore, the pandemic period in recent years increased the moments of social isolation and mobility restriction, perhaps contributing to accentuating the few exercise habits in this population. At the same time, this created an opportunity to develop and investigate new interventions that are suitable for this new scenario, allowing a safe and viable treatment alternative for this population (e.g., online practice). Most studies with exercise in patients with fibromyalgia are carried out face-to-face. Therefore, this randomized controlled trial protocol aims to structure a study protocol to verify the effects of strength training without external material that will be applied online over a short period (8 weeks), on balance, neuromuscular performance, and symptomatology of fibromyalgia. It is expected that the protocol can be used as a basis and/or an initial protocol for future interventions to clarify and assist the effects of fibromyalgia.

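### The only signed standardised effect size (Cohen) is an intra-group one, and the plan does not say which contrast carries the conclusion about training

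*Protocol article*

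**What the plan says.** The Introduction states the aim as follows: "verify the effects of strength training without external material that will be applied online over a short period (8 weeks"). The outcomes it names are balance, neuromuscular performance and symptoms. For this the trial randomises 1:1 against a control group with no activities (section 2.4), whose members are "instructed to maintain their usual medical treatment and daily routines" (section 2.7.2). Both arms are re-evaluated after the 8 training weeks and again after 4 weeks off training (section 2.5). With baseline, that makes three assessments.

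For normally distributed data, section 2.10 plans that "inter-group and intra-group differences will be calculated by repeated measures analysis of variance (ANOVA"). On effect sizes it says: "To calculate the effect size, Cohen's test (intra-group comparison) will be used, and the between-group variance (partial eta squared) will be estimated". One significance level of 0.05 covers everything. No term of the ANOVA (group, time, or group by time) is named as the test of training.

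Section 2.9 sizes the trial for a "moderate effect size (partial eta squared of 0.09) in the intra/inter-group comparison", again without separating the two, and concludes that "the total number of participants should be 24 so that the power of the results is 90"%.

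**The concern.** An intra-group comparison tests whether an arm changed over time. The trial's question is whether the arms differ in how much they changed. Change inside the trained arm combines any training effect with regression to the mean, natural course, usual care, expectancy in participants who know they are training, and practice on repeated jump, throw and balance tests. The control arm is there to remove these components, and an intra-group Cohen value does not use it.

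Partial eta squared does not fill the gap. It has no sign and no outcome units. For a group-by-time term over three visits it also pools the post-training and off-training assessments, so it cannot say how much was gained after training or how much remained 4 weeks later.

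What is at stake is interpretation. A report that follows 2.10 literally would offer, as its only signed standardised effect, a figure that can look moderate when training does nothing. The pattern of a significant change in the trained arm and none in controls could be mistaken for evidence of a difference between arms.

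**Working it through.** **1. The plan's own sample size, and whether it shows which contrast was meant.**
Inputs from section 2.9: partial eta squared 0.09, alpha 5%, power 90%, N = 24, 20% dropout, 30 recruited. Three measurements (m = 3) follow from section 2.5. The correlation between visits, rho = 0.5, is an assumption.
- f² = 0.09/0.91 = 0.0989, so f = 0.314.
- Noncentrality = f² × N × m/(1 − rho) = 0.0989 × 24 × 3/0.5 = 14.24, with 2 and (24 − 2) × 2 = 44 degrees of freedom.
- Power = 0.914. N = 24 is the smallest even N reaching 90%, and 24/0.8 = 30. The stated figures are reproduced.

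The same formula and the same N = 24 apply to the time effect and to the group-by-time interaction. The sample size therefore does not reveal whether change over time or difference between arms was intended. A between-group main effect over three visits would need 74 (power 0.44 at N = 24).

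**2. What intra-group statistics show when training has no effect.**
Assumptions: normal data, SD 1 at each visit, rho = 0.5, and the same shift from baseline in both arms at both later visits. The true training effect is 0. The shift is not in the documents, so a range is shown.

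The analytic check for the pre-post comparison in one arm runs as follows.
- SD of change = √(2(1 − 0.5)) = 1.
- With n = 12 and shift 0.5, the t noncentrality is 0.5 × √12 = 1.73 on 11 df, which gives a two-sided rejection rate of 0.353.
- The expected d (mean change over baseline SD) is 0.5/0.930 = 0.538, where 0.930 = 1 − 3/(4 × 11 − 1) is the small-sample factor.
- The arms are independent, so the chance of trained significant and control not is 0.353 × 0.647 = 0.228.

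Simulation (20,000 trials per setting) agrees:

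| Per arm | Shared shift (SD) | Mean trained-arm d | Trained-arm paired test rejects | Trained significant, control not | Group by time rejects |
|---|---|---|---|---|---|
| 12 | 0 | 0.00 | 5.1% | 4.8% | 5.0% |
| 12 | 0.2 | 0.22 | 9.8% | 8.8% | 5.1% |
| 12 | 0.3 | 0.32 | 15.5% | 13.1% | 5.2% |
| 12 | 0.5 | 0.54 | 35.0% | 23.0% | 5.0% |
| 15 | 0.2 | 0.21 | 11.1% | 9.7% | 5.2% |
| 15 | 0.5 | 0.53 | 43.6% | 24.4% | 4.9% |

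A separate simulation (6,000 trials per setting) used a one-way repeated measures F test over all three visits in the trained arm, with rho 0.5 to 0.7 and 12 to 15 per arm. Rejection was 9 to 16% at a shift of 0.2 SD and 37 to 69% at 0.5 SD. The group-by-time test stayed at 4 to 6%, and the between-arm standardised difference in change averaged 0.0.

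**3. Precision of the between-arm contrast.**
At 12 per arm and rho = 0.5, the standard error of one arm's mean change is 1/√12 = 0.29 SD. For the difference between arms it is √(2/12) = 0.41 SD, larger by a factor of √2.

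**The case against.** The strongest reply is that the control arm is not ignored. Section 2.10 plans inter-group differences by repeated measures ANOVA, and a two-arm analysis of that kind ordinarily contains the group-by-time term, which holds its 5% level in every setting above. The second half of the effect-size sentence gives a between-group measure. Nothing restricts Cohen's value to the trained arm, so a shared drift would also appear in the control arm's own d, and reported arm means would show direction and amount. Within-arm description also serves section 2.1's question of how long effects persist. All of this stands.

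It limits what can be claimed. A reader might infer that intra-group change will be reported as the training effect, or that significance in one arm but not the other will be the criterion. The article says neither. The rejection rates above are therefore not error rates of a rule the protocol adopts, and with no shared drift the within-arm test stays at about 5%. A reader might also infer that the Introduction's hope of providing a basis for future interventions refers to these effect sizes. It refers to the exercise protocol.

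An unseen analysis plan may name the decisive contrast. But the article does more than leave detail out: it fixes Cohen's measure as intra-group. A plan with a between-arm effect size would differ from 2.10, and the two would need aligning.

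**Conclusion.** The concern holds as a fault in the stated effect measure and in the unnamed contrast. The planned between-group test is not at fault. Section 2.10 ties its only signed standardised effect to intra-group change, leaves an unsigned share of variance between groups, and does not say which comparison carries the conclusion. Under an assumed equal drift of 0.2 to 0.5 SD and no training effect, at 12 per arm and rho 0.5, the trained-arm d averages about 0.2 to 0.5 and the within-arm test rejects in roughly 10 to 35% of trials. The group-by-time test stays near 5%. The direction of the problem does not depend on the assumed values, but its size does, and the documents give neither the drift nor the correlation. The change should be made; it is not grounds for saying that the trial cannot answer its question.

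**What to change.** In section 2.10:
- State that conclusions about training rest on the between-arm difference in change from baseline (group by time).
- Report that difference for each outcome at the post-training visit and at the visit after the off-training weeks, in outcome units with a 95% CI and as a between-arm standardised difference.
- Label intra-group changes and Cohen values as descriptive.

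A small-sample correction to the standardised difference, and dropping within-arm p-values, are optional.

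The cost is wording only, with the same data and visits. Under the reproduction above, N = 24 already gives 0.914 power for group by time at rho 0.5, so this change alone asks for no larger sample on that assumption. The N for 90% power is 32 at rho 0.3 and 16 at rho 0.7. That figure also relies on the effect-size convention used there. If 0.09 is meant as the partial eta squared that SPSS prints for the interaction, the noncentrality is 0.0989 × 22 × 2 = 4.35 and power at 24 is 0.42. The small downside is that reported effects will usually be smaller and less precise than intra-group ones.
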